## Abstract

**Background:**

Insomnia is a prevalent sleep disorder associated with significant economic and personal burdens. Cognitive behavioural therapy for insomnia (CBTI) is considered the gold standard intervention for insomnia and its efficacy has been well demonstrated. However, the core treatment strategies of CBTI require significant behavioural change, which many individuals find challenging. As a result, although CBTI is efficacious, its effectiveness is reduced by modest levels of adherence in typical clinical settings. This is problematic as adherence is essential to attain desired treatment outcomes. Sleep is often a dyadic process, with approximately 60% of Australian adults sharing a bed. Hence, the present study aims to determine whether incorporating bed partners into treatment for insomnia increases treatment adherence and completion. The impact of adherence on symptoms of insomnia will also be examined.

**Methods:**

This study is a mixed-effects randomised effectiveness trial of partner-assisted CBTI (PA-CBTI). It is an “effectiveness” (as opposed to “efficacy”) trial, due to the focus on “real world” clinic-based clients and adherence/attrition as outcomes. Participants will include 120 clients with insomnia who are randomly assigned, in equal numbers, to PA-CBTI, traditional individual CBTI (i-CBTI), or partner-assisted sleep management therapy (PA-SMT; which serves as the control group). All interventions consist of seven weekly 1-h sessions. Treatment outcome is evaluated using clinician-rated treatment adherence, and diary-based adherence to stimulus control and sleep restriction. Clients and partners complete major assessments at pre- and post-treatment, and at 6-month follow-up. Secondary outcome variables include actigraphy, self-report measures related to sleep, comorbid psychopathology, and relationship functioning.

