### Participants

Study participants (*n* = 120 completers) are clients and their partners recruited from the Monash Healthy Sleep Clinic (Melbourne, Australia) and the community via advertisement, e.g. radio, newspaper, flyer drops, and social media. Our estimated recruitment numbers shown in Fig. 1 are based on a 4:1 referral-to-screening ratio, and our initial screening visit goal assumes a 20% screen failure rate. Our randomisation numbers assume 20% attrition. These rates are similar to those we have experienced in other similar insomnia trials.

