#### Power considerations

We have powered the study for Hypothesis 1A. Hypotheses 1A tests the outcome (i.e. adherence) related to what makes PA-CBTI unique from traditional CBTI. Given the relatively small sample size of our pilot PA-CBTI data (unpublished), we have benchmarked our power analysis to find a medium effect (Cohen’s f = 0.25) in a 3 × 5 (group × session) multivariate analysis of variance (MANOVA) (five sessions, as there are no adherence data in weeks 1 or 2). With alpha = 0.05 and a two-tailed test, a sample size of 120 (40 per group) provides a power of 0.81 to detect a significant effect. Follow-up comparisons also have adequate power [55].

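### 120 is given both as the number randomised and as the number of completers, and the power statement does not say which it uses or support its claim about follow-up comparisons

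*Protocol article*

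**What the plan says.** Three places in the protocol article give the sample size.

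- Abstract, Methods: "Participants will include 120 clients with insomnia who are randomly assigned, in equal numbers" to the three arms.
- Participants: "Study participants (*n* = 120 completers) are clients and their partners", followed by "Our randomisation numbers assume 20% attrition".
- Power considerations: the calculation targets a "medium effect (Cohen’s f = 0.25") in a 3 × 5 group-by-session MANOVA. "With alpha = 0.05 and a two-tailed test", it reports that "a sample size of 120 (40 per group) provides a power of 0.81 to detect a significant effect".

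Power considerations then closes with "Follow-up comparisons also have adequate power". It gives no pairwise effect size, alpha or power for those comparisons. The section on PA-SMT names PA-CBTI against i-CBTI, on adherence and attrition, as the main goal. Statistical tests of hypotheses makes that contrast a follow-up to a significant main effect of group.

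**The concern.** The abstract and the Participants section cannot both be right. With 20% attrition, 120 is either the number entering randomisation or the number finishing, and Power considerations does not say which.

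The distinction matters in this trial. Treatment completion is itself an outcome (Hypothesis 1B), so loss between randomisation and completion is expected and studied. A team working from the abstract could stop recruitment 30 clients early and still report 0.81.

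The comparison that carries the main conclusion is also a pairwise one. The only power figure given belongs to the three-group test, so the word adequate has nothing behind it that a reader can check.

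**Working it through.** **Inputs from the document.** N = 120 (40 per group), f = 0.25, alpha 0.05, three groups, five sessions (Power considerations); attrition 20% (Participants).

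**Inputs assumed here.** The correlation between sessions (rho) and the pattern of the three arm means; neither is stated.

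**1. Randomised against completers.**
- 120 completers at 20% attrition: 120/0.8 = 150 randomised, 50 per arm.
- 120 randomised at 20% attrition: 120 × 0.8 = 96 completers, 32 per arm.
- The gap is 150 − 120 = 30 randomised clients, or 120 − 96 = 24 completers.

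**2. Reproducing 0.81.** For the group main effect in a repeated-measures model, power comes from a noncentral F with 2 and N − 3 degrees of freedom and noncentrality

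lambda = f² × N × 5 / (1 + 4 rho).

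At N = 120 the numerator is 0.0625 × 120 × 5 = 37.5.

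| rho | Power, N = 120 | Power, N = 96 |
|---|---|---|
| 0.5 | 0.89 | 0.80 |
| 0.6 | 0.84 | 0.75 |
| 0.7 | 0.80 | 0.70 |
| 0.8 | 0.76 | 0.65 |

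Power of 0.81 at N = 120 needs lambda of about 10.13, that is 1 + 4 rho = 37.5/10.13 and rho of about 0.68. The stated figure is thus reachable, but only by back-solving for a value that the article does not give. A multivariate (Pillai) test with an effect of the same nominal size comes close by another route: 0.83 with three responses and 0.78 with four.

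**3. Power if 120 is the number randomised.** Lambda is proportional to N, so at 96 it is 10.13 × 96/120 = 8.10. With 2 and 93 degrees of freedom, power is 0.71. Within this model the result does not depend on knowing rho, because 0.81 at N = 120 already fixes lambda. The Pillai variants fall by a similar amount (0.83 to 0.72, and 0.78 to 0.66). This step assumes that only completers contribute to the analysis.

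**4. PA-CBTI against i-CBTI.** Suppose both partner arms are equal and lie above i-CBTI by d. The standard deviation of the three means is then d × √2/3. Setting this to 0.25 gives d = 0.25 × 3/√2 = 0.53. The variance of a five-session mean is (1 + 4 × 0.676)/5 = 0.74 of that of a single session, so the standardised difference is 0.53/√0.74 = 0.62. With a two-sample t test at two-sided 0.05, unadjusted and at the rho that reproduces 0.81:

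| Pattern of means | d | 40 per arm | 32 per arm |
|---|---|---|---|
| Partner arms equal, i-CBTI lower | 0.53 | 0.78 | 0.68 |
| PA-CBTI and i-CBTI at the extremes, evenly spaced | 0.61 | 0.88 | 0.80 |
| PA-CBTI and i-CBTI adjacent, evenly spaced | 0.31 | 0.35 | 0.29 |

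**The case against.** The strongest reply is that the body of the article settles which 120 is meant. Participants speaks of completers and says that attrition was allowed for, and Power considerations uses 120 with 40 per group. Together these point to 120 analysed and about 150 randomised, with the abstract loosely worded. Fig. 1, which carries the anticipated numbers, could not be read here. This reply largely stands. The abstract still contradicts the body, and the power section still leaves its 120 unlabelled.

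A reader might go further and infer that the stated power is wrong. The document does not support that. Without the correlation, 0.81 can be neither confirmed nor refuted, and if 120 is the number analysed, the 20% attrition does not undermine it. The fact that 96 clients give 0.80 at a correlation of 0.5 is no defence of the smaller sample, however: that correlation gives 0.89 at 120, which is not the figure stated.

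A reader might also infer that the main pairwise comparison is shown to be underpowered. That too goes beyond the text. The research aims expect better adherence in the partner-assisted arms, and the PA-SMT section expects high adherence there, but neither says that the two partner arms are equal. The Sleep diaries section notes that sleep restriction and stimulus control are not recommended in PA-SMT, so its scores on those measures need not match. The article also sets no threshold for adequate, and 0.78 is only slightly below the conventional 0.80.

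Three harsher calculations are tempting but are not the trial's own design: power on a single session's score (the design has five sessions), a halved alpha for two comparisons (no split is stated), and the 33–39% dropout cited in the Background from other clinical settings (the planned 20% rests on the team's own similar trials).

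**Conclusion.** The contradiction over 120 holds and needs no assumption: the abstract and the Participants section differ by 30 randomised clients. Its effect on power is conditional. If the abstract were followed literally and only completers were analysed, the stated 0.81 would become about 0.71. If the Participants section governs, as is more likely, 0.81 at 120 analysed stands as an unverified figure that needs a between-session correlation of about 0.68 under a repeated-measures between-group model.

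The claim about follow-up comparisons is unsupported rather than shown false. Given the stated 0.81, power for PA-CBTI against i-CBTI at 40 per arm is about 0.78 under the pattern that the aims suggest, with a range of 0.35 to 0.88 over the other patterns tried. The mean patterns are assumptions made here.

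**What to change.** 1. In the abstract, give about 150 clients randomised (50 per arm) to obtain 120 completers, matching the Participants section.
2. In Power considerations, say that 120 (40 per group) is the number analysed. If only 120 are in fact randomised, restate the power as about 0.71 for 96 completers.
3. State the between-session correlation and the model behind 0.81.
4. Replace the sentence on follow-up comparisons with the assumed pairwise effect, the alpha used and the resulting power for PA-CBTI against i-CBTI, naming the mean pattern on which it rests.

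If about 150 are being randomised, as the Participants section implies, the cost is wording only. The one downside is that the stated figures may become slightly less favourable.

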**Discussion:**

This is the first randomised clinical trial to examine the impact of incorporating the bed partner in the treatment of insomnia. Results will provide new information about the role partners play in clients’ insomnia presentation and treatment response, and better define the role of adherence in CBTI. This trial has the potential to optimise treatment outcomes for insomnia by improving adherence and reducing attrition. Results could have far-reaching impacts. Improvements in insomnia have been linked to improvements in mental and physical health and, given the high financial costs of insomnia, this study could have a positive economic impact.

**Trial registration:**

ACTRN, ACTRN12616000586415. Registered on 5 May 2016.

**Electronic supplementary material:**

The online version of this article (10.1186/s13063-019-3334-3) contains supplementary material, which is available to authorized users.

## Background

### The impact of insomnia

Insomnia is a highly prevalent and impairing sleep disorder, affecting 10–15% of adults worldwide [1–5]. In Australia, 34.5% of the adult population report regular difficulty falling asleep or staying asleep, hallmark symptoms of insomnia, and many develop a diagnosable insomnia disorder [6]. Insomnia is associated with substantial personal and economic costs. Individuals with insomnia report lower quality of life [7], are at greater risk of accidents [8–11], and have high rates of psychiatric comorbidities [1]. For example, in Australia from 2009 to 2010, half of the clients seen for depression in General Practitioners’ offices also presented with insomnia [12]. In addition to depression, individuals with insomnia are more likely to develop a range of mental health issues, including suicidality, substance abuse, and post-traumatic stress disorder (PTSD), as well as physical health problems such as hypertension, diabetes, and cardiac events [6]. Insomnia carries substantial economic burden ($10.9 billion in Australia in 2010) due to high healthcare costs, reduced work productivity, and increased accidents both at work and on the road [6].

### Behavioural interventions for insomnia

There is a strong evidence base for the non-pharmacological treatment of insomnia [13, 14] with behavioural intervention [15]. Cognitive behavioural therapy for insomnia (CBTI) has been identified as the gold standard intervention for treating insomnia. CBTI is a multi-component intervention based on Speilman’s behavioural model of insomnia [16]. CBTI is efficacious in the short-term; individuals maintain therapeutic gains at long-term follow up, and research indicates its long-term superiority to pharmacotherapy in several randomised controlled trials [17, 18]. Treatment effects are seen in primary and comorbid insomnia [19]. Furthermore, CBTI produces greater subjective and objective sleep improvements when compared with no treatment, progressive relaxation therapy, and pharmacologic and non-pharmacologic placebo interventions [20]. CBTI also has a number of practical advantages: it is relatively brief (i.e. seven to eight sessions on average), can be delivered effectively in multiple formats (e.g. individual or group [20]), and is generally preferred by clients over medications [18].

### The importance of adherence and attrition

Dismantling studies have shown that the two components carrying the most variance in treatment outcomes in CBTI are sleep restriction therapy (SRT) and stimulus control (SC) [21]. SRT requires the individual with insomnia to stay up much later and/or get out of bed much earlier than they typically do; this builds sleep pressure, in essence by sleep depriving clients. SC requires getting out of bed when the individual is unable sleep, something many individuals find very difficult in the middle of the night. Both strategies are challenging and require significant effort to maintain adherence. Therefore, while CBTI is efficacious, as with any behavioural intervention, it only produces the desired outcome when the individual adheres to the treatment recommendations and completes the treatment. Although the challenges of sleep restriction and stimulus control are typically overcome in tightly controlled randomised controlled trials (RCTs) due to the added support provided by the study and the typically homogenous sample, they pose a challenge for mainstream clinicians without those added resources and enrolment restrictions.

The two places where the potential difficulties associated with the behavioural changes demanded by CBTI would be expected to diminish outcomes in more real-world settings are: 1) adherence to the treatment protocol; and 2) attrition (i.e. treatment drop-out).

A recent review shows that adherence to CBTI in the clinical settings ranges from 32–52% [21]. The lowest rates were in clinical effectiveness studies and studies with comorbid populations [21]. Not surprisingly, even modest improvements in CBTI adherence can improve outcomes [22]. Findings from a study of 696 clients with insomnia found that those who completed treatment with high adherence improved significantly more than completers with low adherence [22]. Additionally, adherence is the strongest predictor of long-term (e.g. 1 year) outcomes [22]. Attrition also reduces the benefits of treatment, especially in clinical settings where dropout rates are reported to be as high as 39% [23, 24]. A study on the national dissemination of CBTI in the US Veteran Affairs Healthcare System reported that 33% of clients dropped out [24]. Together, these studies suggest a sizable proportion of clients are likely not to be fully benefiting from CBTI. Efforts to broadly implement CBTI would benefit from ways to improve treatment adherence and completion rates. There currently are no evidence-based recommendations for augmenting either treatment adherence or completion in CBTI.

### Partner-assisted interventions: increasing adherence and completion

One attractive option for increasing adherence and completion in CBTI is via the involvement of bed partners due to 60% of Australian adults sharing a bed. A growing body of literature supports the effectiveness of couple-based interventions for treating individual psychiatric disorders including mood, obsessive compulsive disorder, PTSD, eating disorders, and substance-related disorders [25–28]. Within the sleep field, qualitative studies have suggested including the bed partner in continuous positive airway pressure treatment for sleep apnoea [29, 30]. In “partner-assisted” interventions, partners play a supportive role by acting as surrogate therapists, helping clients make behavioural changes outside of the therapy setting [31]. Treatment focuses on improving the client’s symptoms without directly targeting the couple’s relationship [32]. Partners in this role are taught to help provide an environment favourable to behaviour change and to reinforce positive client changes [32]. This is important, because well-intentioned partners can negatively impact clients’ psychiatric conditions and treatment gains [32]. For example, caring partners can inadvertently accommodate clients’ maladaptive behaviours in an effort to demonstrate support, avoid conflict, or decrease distress for clients or themselves. Such accommodation can often reinforce maladaptive behaviours and work against treatment goals [32]. Therefore, the need to educate partners may well be relevant in insomnia.

To our knowledge, the only partner-assisted intervention for insomnia to be tested was performed by the investigator team during the treatment development phase prior to the current RCT. Thus, this study aims to determine whether enlisting partner support in adhering to difficult behaviour change, and teaching partners to reduce ineffective, albeit well intentioned, accommodating behaviours, could serve to optimise important environmental and behavioural conditions in the treatment of insomnia.

### Couples and sleep

The literature on couples and sleep is relatively sparse, especially in the context of insomnia. However, recent reviews and the few observational studies in this domain highlight several important points. Importantly, sleep is often a social experience since the majority of adults have bed partners [33]. Consistent with this idea, couples prefer to sleep in the same bed and report worse sleep when they sleep alone, despite objective evidence for negative consequences on sleep from co-sleeping [34]. Moreover, couples influence each other’s sleep. For example, Lee et al. found sleep duration covaried within couples on a daily basis, and sleep quality covaried within couples when averaged across several days [35]. Sleep is also related to relationship satisfaction. For example, Troxel et al. found sleep disturbance, including insomnia, and relationship satisfaction were associated [33]. Similarly, those with sleep-onset insomnia were more likely to report relationship problems as a result of their own or their partner’s sleep issues [36]. Another study found higher marital satisfaction was linked to higher sleep-wake concordance in couples [37], and a large study (*n* = 405 couples) found a spouse’s sleep problems predicted higher levels of marital unhappiness [38]. Finally, couple-level variables, including bed partner behaviours, can perpetuate insomnia [34]. For example, bed partners can encourage a client to sleep in or take a nap after a bad night of sleep, or to read, watch TV, etc. in bed until they become sleepy, or they can increase a client’s attentional preoccupation with sleep by asking about their sleep in the morning. While these behaviours are generally well-intended, they are all antithetical to treatment. Therefore, evidence suggests that partners affect each other’s sleep and relationship satisfaction, and thus incorporating a partner into CBTI has the potential to significantly impact outcomes. Surprisingly, though, no published studies report development or testing of a CBTI intervention incorporating the partner.

## Research aims and hypotheses

Finding ways to maximise treatment effectiveness in insomnia is of paramount importance. The present study’s broad aim is to increase adherence to and completion of CBTI. We will endeavour to do this using partner-assisted CBTI (PA-CBTI), a novel strategy which incorporates the bed partner in the intervention. We will systematically assess the value added by including the partner in the intervention. PA-CBTI will be compared with two control treatments (individual CBTI (i-CBTI) and partner-assisted sleep management therapy (PA-SMT)). The present study’s hypotheses are based on the premise that: (a) including the partner will increase adherence to treatment recommendations; and (b) the active ingredients of CBTI are required for good clinical outcomes. Thus, we expect the partner-assisted interventions to show better adherence, the CBTI interventions to show better outcomes, and only PA-CBTI to show both.

### Aim 1

To examine the impact of adding the partner to treatment on adherence and completion.

#### Hypothesis 1A

Participants in the partner-assisted treatment will show better treatment adherence to SRT and SC, measured by daily sleep diaries and greater overall adherence on clinician-rated adherence forms, relative to those receiving individual CBTI.

#### Hypothesis 1B

Participants in the partner-assisted treatment will evidence higher treatment completion rates than i-CBTI.

### Aim 2 (secondary outcomes)

To examine the impact of adherence on insomnia symptoms in the short- and long-term (6 months post-treatment completion). This will test if adherence is directly related to outcomes and if the combined effects of the partner and CBTI are superior to either alone.

#### Hypothesis 2A

In PA-CBTI and i-CBTI, but not PA-SMT, adherence will be positively associated with diary-based sleep efficiency at post-treatment assessment.

#### Hypothesis 2B

Due to increased adherence, sleep outcomes will be better at 6-month follow-up in PA-CBTI relative to i-CBTI.

## Methods

This study is a mixed-effects randomised effectiveness trial of partner-assisted CBTI (PA-CBTI). It is an “effectiveness” (as opposed to “efficacy”) trial, due to the focus on “real world” clinic-based clients and adherence/attrition as outcomes. Participants are randomly assigned, in equal numbers, to PA-CBTI (the active treatment group), or to one of the two control conditions: traditional individual CBTI (i-CBTI) or partner-assisted sleep management therapy (PA-SMT). A flow chart of enrolment, allocation of treatment, and follow-up is presented in Fig. 1.

**Fig. 1 Fig1:**
[figure not shown]
Standard Protocol Items: Recommendations for Interventional Trials (SPIRIT) diagram for enrolment, allocation, follow-up, and analysis. Participant numbers noted are those anticipated, not those currently enrolled/completed. CBTI cognitive behavioural therapy for insomnia, I individual, PA partner-assisted, SMT sleep management therapy

